**Figure 1 F1:**
[figure not shown]
Feelix Smartscope.

### Objectives and hypotheses

The primary objectives of the study are:

to assess whether lung sounds recorded using the Feelix Smart Stethoscope in children by health workers at community-level health facilities meet predefined quality thresholds established by experts; andto determine the reliability and performance of the Smartscope Respiratory Detector automated analysis algorithm on lung sounds recorded by community healthcare provider (CHCP) using the Smartscope, compared with reference interpretations by a paediatric listening panel.

The study hypotheses are:

More than 50% of patients will have ‘quality’ lung sound recordings (targeted goal), defined as at least 75% interpretable lung sound segments per patient (ie, 3 out of 4 chest positions).The agreement between automated computerised analysis (respiratory detector) and paediatric listening panel will be high (kappa >0.8).

## Methods and analysis

### Study setting

This study will be implemented in the Projahnmo field site, a site for maternal, new-born and child health research, which was established in 2001 in Sylhet district of Bangladesh by a partnership of Johns Hopkins University, the Bangladesh Ministry of Health and Family Welfare (MOHFW) and several Bangladeshi institutions, including non-government organisations and academia. A well-established routine community-based pregnancy, birth and under-5 child surveillance system are being maintained by trained female community health workers (CHWs) in this site. The CHWs identify sick children during routine household visits and refer the children to the health facilities. They also educate carers of children about pneumonia signs and symptoms, so that the carers can visit nearby community clinic (CC) without delay.

Bangladesh has established about 13 000 CCs, one each for ~6000 people.^39^ Each CC is staffed by a CHCP with at least 12th grade education and 3 months of preservice training, including IMCI guidelines. Each CHCP is responsible for providing primary healthcare for the population, including its catchment area’s children. Nine CCs will be purposively selected from the Projahnmo surveillance area (Zakiganj sub-district of Sylhet district of Bangladesh) (figure 2). CHCP of respective CC will screen all under-5 children while providing primary healthcare.

**Figure 2 F2:**
[figure not shown]
Study site.

All CHWs and CHCPs will be trained and standardised to identify signs and symptoms of pneumonia according to WHO IMCI guidelines. A study physician will be recruited for providing training and supervision of CHCPs and CHWs in clinical assessments, measurement of peripheral oxyhaemoglobin saturation (SpO_2_) and recording of lung sounds using the Smartscope. However, the study physician will not be directly involved in recording lung sound from the study participants.

### Study design and procedure

Using a cross-sectional design, each CHCP will screen all children younger than 5 years consecutively visiting the CC. CHCP will obtain consent and record lung sounds of children who will fulfil the following criteria: history and/or observed cough and/or history and/or observed difficult breathing and a permanent resident of the Projahnmo site and not enrolled in the study within the past 30 days. CHCP will record sounds from four chest locations—two from the back and two from the front (figure 3). Each position will be recorded for approximately 10 s and the overall recording process will take about 1 min. The recorded sound files will be then transferred to a password-protected server. CHCP will also examine the child for fast breathing by manually counting respirations and observe for abnormal breathing patterns such as lower chest wall indrawing, nasal flaring, head nodding, tracheal tugging, grunting, intercostal retractions and stridor when calm. CHCP will measure the SpO_2_ using a Masimo Rad5 pulse oximeter, temperature using a digital thermometer and anthropometry (weight, height and mid-arm circumference) using standard tools and techniques. The SpO_2_ data will be used to classify pneumonia according to IMCI guidelines. If any child has a SpO_2_ <90%, then referral to the subdistrict health centre or Sylhet Osmani Medical College Hospital will be initiated. All enrolled children will be assessed after day 8 of enrolment by Projahnmo CHWs for treatment compliance and treatment outcome.

**Figure 3 F3:**
[figure not shown]
Lung sounds recording positions.

A total of 11 paediatricians will be trained to the methodology developed and validated during the Pneumonia Etiology Research for Child Health (PERCH) study.^40^ Only paediatricians successfully standardised to the methodology will serve as human listening panel members. Panellists will classify the recorded sound files of all four positions separately into five categories, for example (1) no wheeze and no crackles, (2) wheeze only (no crackles), (3) crackles only (no wheeze), (4) both wheeze and crackles or (5) uninterpretable. Two primary listeners will independently classify the recorded lung sounds, and any discrepancies will be arbitrated by the third listener ([name]). The panellists and [name] will be blinded to the clinical information of the children. Johns Hopkins and Sonavi Labs developed a machine learning algorithm; all sound files will also be classified the same categories using this algorithm. This algorithm does not include the clinical information of the children and this will be blinded to the panel classification. Finally, both classification will be compared. Figure 4 depicts the study flow.

**Figure 4 F4:**
[figure not shown]
Study flow.

### Sample size calculation

Cohen’s kappa will be used to assess interlistener and computer–human agreement in this study. To detect a true kappa of 0.50 compared with a kappa of 0.40 under null hypothesis and assuming two-sided type I error of 5%, power of 80% and two categories of frequencies equal to 30% and 70% normal and abnormal findings, respectively, a sample size of 752 will be required.^41^ This sample size has been calculated in Power Analysis and Sample Size software V.11.

We will include all quality recordings for this assessment. A quality recording is defined as a recording with >75% interpretable chest positions (ie, three of the four chest positions recorded are interpretable). Assuming that 75% of all recordings will be of acceptable quality, we will need 1003 subjects to be enrolled in this study to obtain our required sample size of 752.

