### Statistical analysis

A point estimate for the proportion of recordings along with a 95% CI that meets the definition of quality will be determined. The numerator will be the total number of recordings that were interpreted to meet quality criteria and the denominator will be the total number of recordings collected and interpreted. A raw agreement percentage will be determined between the interpretations of the two primary human listeners of the listening panel. The numerator will be the total number of recordings with an interpretation from the first and second human listener that agree, and the denominator will be the total number of recordings that have a final human interpretation from both primary listeners. Cohen’s kappa, a metric that assesses the agreement beyond chance will be calculated, and a kappa adjusted for prevalence and bias will also be calculated. A kappa above 0.8 will be defined as perfect agreement, 0.61–0.8 as high agreement, 0.41–0.6 as moderate agreement, 0.21–0.4 as fair agreement, 0.01–0.2 as low agreement and 0 as no agreement.

A raw agreement percentage between the overall human listening panel’s final interpretation result and the computerised analysis algorithm’s final interpretation result will be determined. The numerator will be the total number of recordings with an interpretation from the human listening panel and the computerised algorithm that agree, and the denominator will be the total number of recordings that have both a human and computerised interpretation. Cohen’s kappa, a metric that assesses the agreement beyond chance will be calculated, and a kappa adjusted for prevalence and bias will also be calculated. The same kappa scale detailed previously will be used for interpretation.

The performance of the computerised interpretation algorithm will be evaluated when assuming the human listening panel’s final interpretation is the gold standard. Sensitivity, specificity, positive predictive value, negative predictive value and positive and negative likelihood ratios will be assessed.

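### The 80% power is for kappa 0.50 against 0.40 and does not apply to the study hypothesis that algorithm–panel kappa exceeds 0.8

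*Protocol article*

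**What the plan says.** Under *Objectives and hypotheses*, the second study hypothesis reads: "The agreement between automated computerised analysis (respiratory detector) and paediatric listening panel will be high (kappa >0.8"). It concerns the algorithm against the panel only.

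Under *Sample size calculation*, the article opens with "Cohen’s kappa will be used to assess interlistener and computer–human agreement in this study" and then gives one calculation: "To detect a true kappa of 0.50 compared with a kappa of 0.40 under null hypothesis", "assuming two-sided type I error of 5%, power of 80" per cent, and "two categories of frequencies equal to 30% and 70% normal and abnormal findings, respectively, a sample size of 752 will be required". The enrolment target follows: "Assuming that 75% of all recordings will be of acceptable quality, we will need 1003 subjects to be enrolled". No other sizing appears, and nothing links 0.40 or 0.50 to the 0.8 in the hypothesis.

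Under *Statistical analysis*, kappa and a prevalence- and bias-adjusted kappa are to be calculated and read on a fixed scale: "A kappa above 0.8 will be defined as perfect agreement, 0.61–0.8 as high agreement, 0.41–0.6 as moderate agreement, 0.21–0.4 as fair agreement".

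**The concern.** The hypothesis and the sizing concern the same agreement but use different kappas. At the planning truth of 0.50 the hypothesis is false, and rejecting 0.40 says nothing about 0.8. On the article's own scale, 0.40 is the top of *fair* and 0.50 is *moderate*, while the hypothesis lies above the whole 0.61–0.8 band.

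A reader who sees a hypothesis of kappa above 0.8 and, a few sections later, 80% power will join the two. What is at stake is the claim of adequate power for one of the two primary objectives. Nobody can tell from the article how likely the study is to support its hypothesis, or how precisely it will estimate kappa near 0.8.

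The labels add to the confusion. The hypothesis calls kappa above 0.8 *high*; the analysis section calls it *perfect* and keeps *high* for 0.61–0.8. An observed kappa of 0.70 would be *high* on the scale and would still not meet the hypothesis.

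**Working it through.** **Inputs from the article:** null kappa 0.40, alternative 0.50, two-sided 5%, power 80%, two categories at 30% and 70%, 75% of recordings usable, hypothesis kappa above 0.8. **Assumed here:** independent child-level pairs, both raters with 30/70 margins, and a range of true kappas, because the article gives none.

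**1. Reproduce the plan's figure.** The large-sample variance of a two-category kappa with equal margins is V(k)/n, where

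V(k) = (1 − k)[(1 − k)(1 − 2k) + k(2 − k)/(2pq)], with p = 0.3, q = 0.7, 2pq = 0.42.

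- V(0.40) = 0.6 × [0.6 × 0.2 + 0.4 × 1.6/0.42] = 0.986
- V(0.50) = 0.5 × [0 + 0.5 × 1.5/0.42] = 0.893
- n = [(1.96 × √0.986 + 0.8416 × √0.893)/0.10]² = 751.7, so 752
- 752/0.75 = 1002.7, so 1003

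Both stated figures reproduce exactly.

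**2. What the planning alternative implies for the hypothesis.** At kappa 0.50 the SE with 752 pairs is √(0.893/752) = 0.0345. The value 0.80 lies (0.80 − 0.50)/0.0345 = 8.7 SEs above it. If the planning alternative were true, the chance of supporting the hypothesis would be essentially nil.

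**3. Precision near 0.80.** V(0.80) = 0.2 × [0.2 × (−0.6) + 0.8 × 1.2/0.42] = 0.433. The SE is √(0.433/752) = 0.0240, and the 95% half-width is 1.96 × 0.0240 = 0.047.

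**4. Power for the hypothesis.** The article fixes no success rule, so two usual ones are shown. In both, power = Φ[(k − c)/SE(k)], where c is the observed kappa needed.

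- *Confidence-limit rule:* the lower limit of the two-sided 95% CI exceeds 0.80. Solving c − 1.96 × √(V(c)/752) = 0.80 gives c = 0.842, where the SE is 0.0216 and 1.96 × 0.0216 = 0.042.
- *Null-variance test:* the SE is taken at kappa 0.80, so c = 0.80 + 1.96 × 0.0240 = 0.847.

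| True kappa (assumed) | SE at n = 752 | Power, confidence-limit rule | Power, null-variance test |
|---|---|---|---|
| 0.82 | 0.0229 | 17% | 12% |
| 0.85 | 0.0211 | 64% | 56% |
| 0.86 | 0.0204 | 81% | 74% |
| 0.90 | 0.0174 | >99% | >99% |

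Power reaches 80% at a true kappa of about 0.86 under the first rule and about 0.864 under the second.

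**5. If support means only a point estimate above 0.8.** The chance is Φ[(k − 0.80)/SE(k)]: 50% at a true kappa of 0.80, about 99% at 0.85 and essentially nil at 0.50. The stated 80% does not describe this rule either.

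**The case against.** Three arguments can be made for the plan as it stands.

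*The analysis is estimation, not a test.* The analysis section plans no test against 0.40. It reports kappa and reads it on a fixed scale, under which 0.5 has to be called moderate. This stands. A reader might infer that the study could reject 0.40 and present that as confirmation of its hypothesis; the article does not support that inference. The hypothesis still carries a threshold, though, and the only power figure in the article does not belong to it.

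*A low kappa is a cautious planning value for two agreements at once.* For precision this is fair: the SE is 0.034 at kappa 0.50 and 0.024 at 0.80, so the estimate will be tighter if agreement is high. But the article does not give that reason, and for showing that kappa exceeds 0.8 the choice is not cautious, since power is below 20% at a true kappa of 0.82 under either rule. The calculation may have been meant for the interlistener comparison, but the text says it covers both.

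*The sample has not been shown to be inadequate.* This also stands. A reader might infer from the mismatch that 752 is too few, or was miscalculated. The arithmetic is right, and adequacy depends on a true kappa that the article does not state: 752 suffices at about 0.86 or above and falls short below that.

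**Conclusion.** The point holds as a mismatch between justification and hypothesis. The 80% power applies to kappa 0.50 against 0.40, and no power or precision is stated for algorithm–panel kappa above 0.8. Under either rule the real position runs from low power just above 0.80 to near certainty at 0.90, crossing 80% at about 0.86.

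These figures rest on 752 independent child-level pairs, two categories and 30/70 margins. The article has panellists classify four chest positions separately into five categories. If kappa is computed by position or on more than two categories, the SEs and powers do not carry over.

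It should be fixed, but it is not critical: neither the number of recordings, nor enrolment, nor the planned estimates have to change.

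**What to change.** 1. Keep 752 and 1003. State which agreement the 0.40 v 0.50 calculation serves; if it is the interlistener comparison, say so and give that comparison its own hypothesis.
2. For the algorithm–panel hypothesis, choose one of these and quote only its figures:
   - supported if the lower limit of the two-sided 95% CI exceeds 0.80: an observed kappa of about 0.842 is needed; power about 17%, 64%, 81% and over 99% at true kappa 0.82, 0.85, 0.86 and 0.90;
   - a test using the null variance at 0.80: about 0.847 is needed; power about 12%, 56%, 74% and over 99% at the same values;
   - a precision statement: 95% half-width of about 0.047 at kappa 0.80.
3. State the assumptions beside the figures: unit of analysis, number of categories and margins.
4. Present them as what the existing sample delivers, not as the origin of 752. The article records that data collection began in November 2019, so a new derivation of the same number would be back-fitting.
5. Use one label for kappa above 0.8 in the hypothesis and in the interpretation scale.

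The cost is rewording in the hypothesis, sample size and analysis sections. No more children are needed. The drawback is that the power statement becomes less favourable: 80% is reached only if true agreement is about 0.86 or better.

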### Statistical analysis

A point estimate for the proportion of recordings along with a 95% CI that meets the definition of quality will be determined. The numerator will be the total number of recordings that were interpreted to meet quality criteria and the denominator will be the total number of recordings collected and interpreted. A raw agreement percentage will be determined between the interpretations of the two primary human listeners of the listening panel. The numerator will be the total number of recordings with an interpretation from the first and second human listener that agree, and the denominator will be the total number of recordings that have a final human interpretation from both primary listeners. Cohen’s kappa, a metric that assesses the agreement beyond chance will be calculated, and a kappa adjusted for prevalence and bias will also be calculated. A kappa above 0.8 will be defined as perfect agreement, 0.61–0.8 as high agreement, 0.41–0.6 as moderate agreement, 0.21–0.4 as fair agreement, 0.01–0.2 as low agreement and 0 as no agreement.

A raw agreement percentage between the overall human listening panel’s final interpretation result and the computerised analysis algorithm’s final interpretation result will be determined. The numerator will be the total number of recordings with an interpretation from the human listening panel and the computerised algorithm that agree, and the denominator will be the total number of recordings that have both a human and computerised interpretation. Cohen’s kappa, a metric that assesses the agreement beyond chance will be calculated, and a kappa adjusted for prevalence and bias will also be calculated. The same kappa scale detailed previously will be used for interpretation.

The performance of the computerised interpretation algorithm will be evaluated when assuming the human listening panel’s final interpretation is the gold standard. Sensitivity, specificity, positive predictive value, negative predictive value and positive and negative likelihood ratios will be assessed.

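### The quality hypothesis is stated per patient, but the denominator leaves out enrolled children with no recording obtained or none read, so the rate can only be shifted upward

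*Protocol article*

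**What the plan says.** Objectives and hypotheses states the target per patient: "More than 50% of patients will have" quality recordings, where quality is "defined as at least 75% interpretable lung sound segments per patient (ie, 3 out of 4 chest positions").

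The Statistical analysis section sets out the estimator. Its numerator counts the recordings that met the quality criteria. What this count is divided by is put as follows: "the denominator will be the total number of recordings collected and interpreted". A point estimate with a 95% CI is to be reported.

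Two other places bear on how this formula is read:

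- Study design and procedure has the panel classify each of the four positions. One of the five categories is a failure category: "4) both wheeze and crackles or (5) uninterpretable".
- Sample size calculation defines a quality recording over the child's four positions and goes from recordings to children without a further step: "Assuming that 75% of all recordings will be of acceptable quality, we will need 1003 subjects to be enrolled in this study".

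Study design and procedure also bars enrolment only for a child already enrolled in the preceding 30 days, so one child can enter more than once.

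**The concern.** The hypothesis concerns patients, while the formula conditions on two things having happened: a recording was collected, and it was interpreted. Three kinds of enrolled child meet only one of these conditions or neither: a child from whom no recording was obtained, a child whose file was lost between the device and the server, and a child whose file the panel never read. The article does not say that any of them counts as a failure, and the formula as printed leaves them out.

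The Discussion describes the aim as showing that frontline workers can feasibly collect usable lung sounds. For that aim, getting no recording at all is the least favourable result. Leaving such children out can only raise the rate relative to all enrolled children. This is the headline figure for the first primary objective.

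**Working it through.** **Reproducing the plan's figures.** The kappa sample size uses a null of 0.40, an alternative of 0.50, two-sided 5% error, 80% power and marginals of 30%/70%. With the standard large-sample variance for kappa, n = [(z₀.₉₇₅·τ₀ + z₀.₈₀·τ₁)/(0.50 − 0.40)]² gives 752, as stated. Enrolment is 752/0.75 = 1002.67, rounded up to 1003, also as stated. This step takes one recording per enrolled child, which amounts to m = 0. The article gives no sample size for the quality proportion itself.

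**Who is in the denominator under the stated rule.**

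| Enrolled child | Under the stated formula |
|---|---|
| Recording read, three or four positions interpretable | numerator and denominator |
| Recording read, fewer than three positions interpretable | denominator only (a failure) |
| No recording obtained | absent |
| File lost in transfer | absent |
| File never read by the panel | absent |

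**Size of the shift.** Let N be the number enrolled, m the share without a collected and read recording, and r the quality rate under the stated formula. The number of quality recordings is r·N(1 − m). Over all enrolled children the rate is r(1 − m), so the reported rate exceeds it by r·m.

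The documents do not give m, so the values below are assumptions. The 75% is the planning value from Sample size calculation. The 55% is an illustrative value near the target.

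| m (assumed) | 75% becomes | shift (points) | 55% becomes | shift (points) |
|---|---|---|---|---|
| 0% | 75.0% | 0 | 55.0% | 0 |
| 2% | 73.5% | 1.5 | 53.9% | 1.1 |
| 5% | 71.25% | 3.75 | 52.25% | 2.75 |
| 10% | 67.5% | 7.5 | 49.5% | 5.5 |

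**Intervals in whole children, N = 1003 (Wilson 95% CI).**

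- m = 5%: 953 recordings read, 524 of quality. The stated formula gives 55.0% (51.8% to 58.1%). Over all enrolled it is 524/1003 = 52.2% (49.1% to 55.3%).
- m = 10%: 903 recordings read, 497 of quality. The stated formula gives 55.0% (51.8% to 58.3%). Over all enrolled it is 497/1003 = 49.6% (46.5% to 52.6%). The difference from 49.5% in the table is rounding to whole children.

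**When the 50% target is lost.** Setting r(1 − m) = 0.50 gives m = 1 − 0.50/r. For r = 0.75 this is 33.3%, and for r = 0.55 it is 9.1%.

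**The case against.** Much of the case on the other side is sound.

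- A reader might infer that failed recordings are removed from the denominator. They are not. Uninterpretable is a panel category, so a poor recording is collected, interpreted and kept as a failure. The Discussion speaks of crying and agitation as sources of artefact, not of missing files. An incomplete set can also be read, and it fails if fewer than three positions are interpretable.
- A reader might see a serious clash between patients and recordings as units. It is mostly wording, because Sample size calculation treats a recording as one child's set of four positions. Only re-enrolment after 30 days separates the two.
- A reader might say that the sample size uses a different denominator. The 75% there is also expressed as a share of recordings, and the step to 1003 only assumes one recording per child.
- Objective 1, read closely, asks about sounds that were recorded, and the stated formula answers that. This stands as a reason to keep the present proportion. It does not settle hypothesis 1, which speaks of patients.
- A file that was lost or never read might have been a good one. Counting it as a failure measures the whole pathway, not the worker's recording alone. This stands, and it is a reason to report the three kinds of loss separately.
- How missing data are handled is often left to a full protocol or SAP, neither of which is shown. That would answer a gap, but here the article prints the formula, and the formula itself does not match the hypothesis.

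**Conclusion.** The point holds in a limited form. The printed denominator does not match the per-patient hypothesis, and any enrolled child without a collected and read recording shifts the rate upward by r·m. At the planned 75%, an assumed m of 2% to 10% means 1.5 to 7.5 points. If every enrolled child has a recording that is read, the shift is zero.

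A reader might infer that the 50% goal is likely to be declared met when it is not. The documents do not support that. They give no value for m, the Statistical analysis section sets no pass/fail rule beyond an estimate and its CI, and from 75% about one third of enrolled children would have to lack a read recording before the rate fell to 50%. The conclusion is sensitive only near the target: at an observed 55%, m = 5% takes the lower confidence limit below 50%, and m of about 9% takes the point estimate there. The gain from changing the rule is an unbiased feasibility estimate, not a probable reversal.

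**What to change.** Change the definition of the primary quality proportion:

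- **Denominator:** all enrolled children, meaning eligible with consent given. Alternatively use all enrolment episodes, since a child may re-enter after 30 days. State which is used and how repeat enrolments are handled.
- **Numerator:** those with at least three of the four positions read as interpretable by the panel.
- **Counted as not quality:** no recording obtained, file lost, file never read, or fewer than three interpretable positions. Report how many fall in each group.
- **Secondary:** the present proportion among recordings collected and interpreted.

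Writing the numerator as three of four also removes a small inconsistency. Sample size calculation says "A quality recording is defined as a recording with >75% interpretable chest positions (ie, three of the four chest positions recorded are interpretable"), and with four positions a value strictly above 75% would require all four, contrary to its own gloss and to the hypothesis.

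The cost is a sentence or two. The article mentions no enrolment log, but consent and a clinical assessment are planned for every enrolled child, so the count should be available without new data collection. The downside is that the reported rate may be slightly lower.
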